## Abstract

**Background:**

Dental caries is a persistent public health problem with little change in the prevalence in young children over the last 20 years. Once a child contracts the disease it has a significant impact on their quality of life. There is good evidence from Cochrane reviews including trials that fluoride varnish and regular use of fluoride toothpaste can prevent caries.

The Northern Ireland Caries Prevention in Practice Trial (NIC-PIP) trial will compare the costs and effects of a caries preventive package (fluoride varnish, toothpaste, toothbrush and standardised dental health education) with dental health education alone in young children.

**Methods/Design:**

A randomised controlled trial on children initially aged 2 and 3 years old who are regular attenders at the primary dental care services in Northern Ireland. Children will be recruited and randomised in dental practices. Children will be randomised to the prevention package of both fluoride varnish (twice per year for three years), fluoride toothpaste (1,450 ppm F) (supplied twice per year), a toothbrush (supplied twice a year) or not; both test and control groups receive standardised dental health education delivered by the dentist twice per year. Randomisation will be conducted by the Belfast Trust Clinical Research Support Centre ([CRSC] a Clinical Trials Unit).

1200 participants will be recruited from approximately 40 dental practices. Children will be examined for caries by independent dental examiners at baseline and will be excluded if they have caries. The independent dental examiners will examine the children again at 3 years blinded to study group.

The primary end-point is whether the child develops caries (cavitation into dentine) or not over the three years. One secondary outcome is the number of carious surfaces in the primary dentition in children who experience caries. Other secondary outcomes are episodes of pain, extraction of primary teeth, other adverse events and costs which will be obtained from parental questionnaires.

**Discussion:**

This is a pragmatic trial conducted in general dental practice. It tests a composite caries prevention intervention, which represents an evidence based approach advocated by current guidance from the English Department of Health which is feasible to deliver to all low risk (caries free) children in general dental practice. The trial will provide valuable information to policy makers and clinicians on the costs and effects of caries prevention delivered to young children in general dental practice.

**Trial registration:**

EudraCT No: 2009 - 010725 - 39

ISRCTN: ISRCTN36180119

Ethics Reference No: 09/H1008/93:

## Background

Although dental caries is a preventable disease it is a persistent public health problem, with little change in the prevalence in young children over the last 20 years [1]. Caries is closely associated with social deprivation resulting in large geographical and social inequalities across the UK. The last national child dental health survey [1] showed that in 2003 43% and 61% of 5-year-olds in England and Northern Ireland respectively had caries; 10 years earlier, the figures were 45% and 60%. Over the last 10 years the proportion of parents taking children under 3 years to the dentist increased from 42% to 54% [1]; evidently this favourable change in visiting patterns has not been translated into reduced levels of tooth decay in the population.

Few prospective studies have been undertaken to provide an understanding of how the disease behaves longitudinally [2] A recently completed prospective cohort study [2,3] followed 739 children aged 3 to 6 years attending 50 dental practices in the North West of England over a 3 year period. This study demonstrated a stark difference between children who present with and without the disease at their first visit to the dentist. Over the study period 25% of caries free children developed caries, by contrast 72% of those with the disease at initial presentation developed further cavities. No matter what age a child contracted the disease it progressed at the same rapid rate. An important finding of this study was that more cases (children with caries) arose from the initially caries free population (N = 155, 21% of the total population and 25% of the population who were caries free at first attendance) than from those who present with the disease at their first visit to the dentist (N = 118, 16%). NHS Business Services Organisation (BSO) data shows that this situation is mirrored in Northern Ireland; 25% of 2-3-year-old children have the disease at initial presentation but 35% who are caries free at their first visit go on to develop the disease over a 3 year period. Once a child contracts the disease there is a significant impact on their quality of life and that of their family. Children with caries have an 18.8% chance each year of an unscheduled visit due to toothache and an 11% chance of an extraction each year [4]. As adverse outcomes are so common in children with the disease, the priority should be prevention, with a primary focus of maintaining the caries free children in that state. Dentists cannot prevent the disease starting in children who already have caries at their first visit; these children should be considered as a separate population; their dental care needs are quite different and are complicated by the effects of restorative treatment.

The need to improve preventive care provided by dentists has moved up the policy agenda following the publication of the Primary Dental Care Strategy for Northern Ireland [5] in 2006, which placed a strong emphasis on prevention of caries in general practice, and the subsequent Oral Health Strategy for Northern Ireland in 2007 [6], which sets targets for reduction in the caries levels of 5-year-olds. The introduction of new, locally commissioned NHS dental contracts in England and Wales in April 2006 also means that strengthening the evidence base for prevention is important for policy makers and the NHS. One of the main reasons for changing NHS dental contracts was to encourage prevention, however the new contract in England has been heavily criticised by the dental profession and NHS managers [7] and more recently by the House of Commons Health Select Committee [8] for offering little incentive for dentists to provide preventive care. Indeed one of the recommendations of the Health Select Committee report was that 'the Department of Health undertake research to determine the extent to which the provision of preventive advice is being given and its cost-effectiveness.' This emphasis on prevention is also seen in the Darzi report [9] and the Primary and Community Care Strategy [10]. Scotland has decided to retain the centrally funded GDS contract based on capitation for children and fee for item for adults. The Department of Health in Northern Ireland intends to change the GDS contract and wants to use the outcomes of this trial to inform preventive aspects of the new contract. So, there is pressure on politicians, policy makers and NHS commissioners in the UK to ensure that effective caries prevention is provided in practice. Unfortunately recent research suggests that the preventive care currently provided by GDPs is ineffective and inequitable [11]. Dentists are ill-equipped in terms of their knowledge [12] and how they present information to their patients [13] to provide an effective service.

Preventive care provided by most dentists is based on health education aimed at reducing sugar intake [12,13] which lacks evidence to demonstrate its effectiveness [14,15]. However, there is good evidence that fluoride-based interventions can have a dramatic effect on the disease. For example in a systematic review of water fluoridation [16] the median of mean differences of studies suggested that a 15% absolute difference in the proportions of children caries free can be expected between fluoridated and non-fluoridated populations. It has been estimated that this equates to a difference of around 40% in caries increment [17]. In England water fluoridation is currently being examined as a means of preventing caries but is not technically, economically or politically feasible in every area of the UK, so other delivery vehicles such as professionally applied fluoride varnish or distributed fluoride toothpaste need to be considered. A Cochrane systematic review of fluoride varnish [18] included 9 RCTs and reported a pooled d(e/m)fs prevented fraction estimate of 33% (95% CI, 19% to 48%; p < 0.0001). A second systematic review [19] of fluoride varnish used different selection criteria and identified only 3 trials examining primary teeth and concluded that the evidence was inconclusive due to the poor quality of the studies. A subsequently published trial of 2-4 year old children [20] examined the effect of 22,600 ppm varnish applied twice a year over 2 years and reported a 57% reduction in caries increment compared to a control group. Another recent trial in the USA [21] investigated the use of 22,600 ppm varnish on infants with a mean age of 1.8 years resident in an area supplied with artificially fluoridated water at 1 ppm. Caries incidence was lower in those receiving fluoride varnish twice a year than in a counselling only control (OR 3.77 (95% CI 1.88-7.58) and no adverse events were reported.

A Cochrane review of fluoride toothpaste use [22] in children aged 5-16 years reported clear evidence that fluoride toothpastes are efficacious in preventing caries in permanent teeth but there was little information concerning the primary dentition or adverse effects. Similar findings were also reported by another systematic review of toothpastes published around the same time[23]. An RCT in the North West [24] testing fluoride toothpaste provided through the post to children from birth to 5-years-old reported a 16% difference in increment and an 8% absolute difference in the proportion of caries free children receiving 1450 ppm toothpaste compared to a control group. A Cochrane systematic review examined the effectiveness of any fluoride agent (gel, varnish, mouth rinse) combined with toothpaste [25] and reported a D(M)FS pooled preventive fraction of 10% (95% CI, 2% to 17%; p = 0.01) in favour of a combined regimen over toothpaste alone but the significant difference in favour of the combined use of fluoride varnish and toothpaste accrued from a very small trial and appears likely to be a spurious result. The risks associated with these two interventions are small for the age group under investigation. A follow up study [26] of participants in the NW toothpaste trial [24] compared the prevalence of fluorosis in the study groups and reported a slight increase in prevalence of TF score 3 (an index of fluorosis) but no increase in the overall prevalence of developmental defects of enamel. Recent work shows that fluorosis risk is related to an elevated fluoride intake for all of the first 3 years of life [27] but that the first 2 years of life are the period with greatest risk [28].

Although sub-optimal, the available literature has informed the contents of Delivering Better Oral Health an Evidence Based Toolkit [29] national guidance that has been circulated by the Department of Health to every dental practice in England. The fluoride interventions to be investigated in this trial are identified by the Toolkit and the approach taken in this trial; focusing on caries free children is also supported by the Toolkit, which recommends application of the interventions to all children attending dental practice, the majority of whom will be caries free at their first attendance. This reasoning was informed by the outcomes of the North West cohort study [7] and because there are no effective screening tools to accurately and reliable identify the children who will develop caries. The effectiveness of the intervention to be tested and the impact on NHS costs are unknown and need to be tested in primary care.

The aim of this study is to therefore measure the costs and effects of a 'preventive package' of fluoride varnish, fluoride toothpaste, toothbrush and standard dental health education in keeping young children who regularly attend primary care service free of dental caries, compared with receiving standard dental health education alone.

If the technologies tested in this trial are effective at preventing caries and reducing costs it will influence how dentistry is provided for young children both in the UK and internationally. If the interventions are shown not to be an efficient use of resources this will also influence policy and commissioning, to perhaps focus prevention resources on population interventions such as water fluoridation.

## Methods/Design

### Trial Objectives

To compare over a 3 year period the effectiveness of fluoride varnish, fluoride toothpaste, toothbrush and standardised health education, provided twice a year, as a preventive package, with standardised health education alone provided twice a year in preventing the conversion of 2 to 3 year old children from caries-free at baseline to caries-active state in the primary dentition, reducing the number of carious surfaces (caries into dentine) in the primary dentition in children who convert from caries free to caries active states and preventing episodes of pain and extraction of primary teeth.

To compare over a 3 year period the costs of dental care in a group receiving fluoride varnish, fluoride toothpaste, toothbrush and standardised health education, provided twice a year as a preventive package with a group receiving standardised health education alone provided twice a year.

### Study design

NIC-PIP is a pragmatic three year parallel group randomised controlled trial where 2 and 3 year old children are randomised to receive the caries preventive package or not. The recruitment of the children is outlined in Figure 1. A full economic evaluation of the costs of the package is being conducted.

**Figure 1 F1:**
[figure not shown]
**Trial schematic showing the screening, recruitment and randomisation of children**.

### Ethical considerations

Full ethical approval for this study has been obtained from Northwest 7 REC- GM Central (formally Central Manchester Research Ethics Committee). Two external bodies; a Data Monitoring and a Trial Steering Committee, will monitor study progress.

### Study Participants

Participants will be children who are initially aged 2 and 3.99 years who attend NHS General Dental Service (GDS) practices in Northern Ireland. Children will be eligible to participate in the study if they are aged 2 or 3 years, attending the selected GDS practices and a person with parental responsibility signs a consent form. The children will not be eligible if: they have caries into dentine, a past history of fillings or extractions due to caries, fissure sealants on primary molar teeth, history of severe allergic reactions requiring hospitalisation or are already participating in any other clinical trial involving medical products at recruitment.

### Trial interventions

The fluoride varnish (22,600 ppm) is classed as an Investigative Medicinal Product and therefore must comply with relevant UK regulations [30]. The fluoride varnish and toothpaste will appear in its normal commercial packaging. The fluoride varnish will be applied to the dried primary teeth of the children by a participating dentist at two visits to the dental surgery each year at approximately 6 monthly intervals (+/- 4 weeks). One drop of varnish will be applied to the primary teeth in each arch (2 drops in total) using a standardised brush applicator. After application parents will be advised not to brush their children's teeth for 24 hours.

A free toothbrush and a free 50 ml tube of 1,450 ppm of fluoride toothpaste will also be provided to test group children twice a year. Parents of children aged 2 but not 3 years will be advised to use a smear of toothpaste and those over 3 years will be advised to use a pea sized blob of toothpaste when brushing their teeth. Photographs of a smear and a pea size blob will be included in the standardised dental health education guide. It will be stressed to parents that children must be supervised by an adult when they brush their teeth. Standardised dental health education will be given at each 6 month check up visit by dentists following written guidance.

Children allocated to the control group will attend at 6 monthly intervals and receive the same standardised dental health education at each 6 month visit as the test group. The control group will not receive any professionally applied or provided fluoride interventions.

### Follow-up of children

Children will be followed from trial entry until the end of the study (three years). They will attend the dentist every 6 months where data on any symptoms reported or treatment received by each child at each visit (both planned 6 monthly and unplanned symptomatic visits) will be collected on site clinical record forms. A piloted questionnaire for the person with parental responsibility will be used to identify any unscheduled visits to other dental services and other episodes of toothache not severe enough to require a visit to the dentist. Fluoride varnish has been used routinely in dental practice and the risk to participants is low. The reporting criteria for adverse events is shown in Figure 2. The trial manager is undertaking duties delegated by the trial sponsor and is responsible for reporting of Suspected Unexpected Serious Adverse Reactions (SUSARs) and other Serious Adverse Reactions (SARs) to the competent authorities (regulatory authorities and central research ethics committees). The person with parental responsibility, and children, where appropriate, have the right to withdraw from the trial at any time for any reason, and this will be documented.

**Figure 2 F2:**
[figure not shown]
**Flow chart of assessing and notification of Adverse Events**.

### Outcome measures

Baseline and outcome examinations at 3 years will be performed by trained and calibrated examiners. Outcome examiners will be blinded to the treatment allocation and using the same diagnostic protocol. The primary outcome is to measure whether the child has become caries active (caries into dentine). The following secondary outcomes are to be measured on the children: the number of carious surfaces (caries into dentine) in the primary dentition for children who have become caries active, the number of episodes of pain and number of extractions of primary teeth and the costs of dental care over a 3 year period. The final three outcomes will be assessed by questionnaire filled in by the person with parental responsibility.

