### Statistical analysis

All analyses will use an 'intention to treat' principal. All outcome measures stated in the protocol will be fully analysed using generalized linear models adjusting for covariates felt to be of prognostic importance including age and socio-economic status (SES). Statistical significance will be at the 0.05 level for all analysis and 95% confidence intervals will be calculated. A binary logistic regression model will be fitted to the primary outcome, whether the child remained caries free or not, with study group, age and socioeconomic status as covariates. The unadjusted and adjusted odds ratios from the logistic regression model will be reported and will specify that the adjusted is the primary analytical approach. A pre-planned subgroup analysis will be undertaken for deprived/not deprived children by selecting children whose parents are exempt from dental charges or not.

Health economic analysis will compare the total cost to the NHS for dental care in each of the two arms of the trial in accordance with the relative levels of effectiveness for each of the two arms. A multiple linear regression model will be fitted to the individual discounted costs per child with group, age and socio-economic status (SES) as covariates. If the assumptions underlying the model are not upheld, robust estimates of the standard errors will be calculated for the estimated parameters. Separate calculations will be made of between-treatment differences in cost to parents to identify any between-programme trade-offs. All calculations will be subjected to sensitivity analysis and discount rates of 3.5% for both cost and benefits will be applied. The incremental cost effectiveness ratio (ICER) will be estimated by dividing the difference in mean discounted costs between the two groups by the difference in discounted proportions that remain caries free. The relationship between cost and secondary outcomes such as the number of carious surfaces will be examined in an analogous fashion to that detailed above. The net present value of costs will be divided by the net present value of the number of carious surfaces to ascertain the average cost for carious surface avoided.

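### The carious-surface outcome is compared between arms only among children who developed caries, a subset formed after randomisation by the primary outcome, so it cannot be read as an effect on severity

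*Protocol article*

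**What the plan says.** The restriction appears in three places in the protocol article, and they agree.

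- Abstract, Methods/Design: "One secondary outcome is the number of carious surfaces in the primary dentition in children who experience caries".
- Trial Objectives: the package is to be compared with health education alone for "reducing the number of carious surfaces (caries into dentine) in the primary dentition in children who convert from caries free to caries active states".
- Outcome measures: "the number of carious surfaces (caries into dentine) in the primary dentition for children who have become caries active".

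Outcome measures also makes becoming caries active, judged at the 3-year examination, the primary outcome. On entry, the Abstract says: "Children will be examined for caries by independent dental examiners at baseline and will be excluded if they have caries".

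The Statistical analysis section opens with "All analyses will use an 'intention to treat' principal". It then sends every outcome to generalized linear models adjusted for prognostic covariates including age and socio-economic status, with significance at 0.05 and 95% confidence intervals. Its economic part divides costs by the number of carious surfaces to obtain a cost per surface avoided, and does not say whether that count covers all children or only those with caries.

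**The concern.** Randomisation makes the arms comparable at entry. It does not make comparable two subsets picked out at 3 years by something the intervention is meant to change. If the package works, the test-arm cases are the children it failed to protect, while the control-arm cases also include children whom it would have protected. Unless those two kinds of children would have had equally severe disease, a difference in mean surfaces among cases mixes any effect on severity with a difference in who is being counted. Adjustment for age and socio-economic status cannot be relied on to remove differences in unmeasured susceptibility.

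The Trial Objectives word this outcome causally, as a reduction achieved by the package, and the analysis section has it tested. A reader of the results would therefore take the case-only contrast as evidence on severity. It could understate a benefit, suggest harm where there is none, or flatter the package.

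**Working it through.** **Inputs from the protocol article (Sample size considerations):** caries at 3 years 0.47 control and 0.37 test; two-sided 0.05; 90% power; 510 per group; 15% drop-out; 1,200 recruited.

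**The plan's own figure.** With pooled proportion 0.42,

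n = [1.960 × √(2 × 0.42 × 0.58) + 1.282 × √(0.47 × 0.53 + 0.37 × 0.63)]² / 0.10² = 510 per group.

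Then 1,020 / 0.85 = 1,200. The stated design reproduces.

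**Size of the case-only comparison.** Control 510 × 0.47 = 239.7; test 510 × 0.37 = 188.7; together 428.4, or about 42% of 1,020.

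**Who is in it.** Assume the package causes caries in no child. Then 37% of children get caries in either arm, 10% get it only without the package (prevented cases), and 53% never get it. Prevented cases make up 0.10 / 0.47 = 21% of control cases and none of the test cases.

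**Direction of bias.** The article gives no surface means, so these are assumed: mean 6 in children who get caries in either arm, no effect of the package on their severity, and mean m in prevented cases.

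- Control, cases only: (0.37 × 6 + 0.10 × m) / 0.47. Test, cases only: 6.
- Control, all children: 0.37 × 6 + 0.10 × m. Test, all children: 0.37 × 6 = 2.22.

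| Assumed m | Control cases | Test cases | Case-only difference | Control, all | Test, all | All-children difference |
|---|---|---|---|---|---|---|
| 1 | 4.94 | 6.00 | +1.06 | 2.32 | 2.22 | -0.10 |
| 2 | 5.15 | 6.00 | +0.85 | 2.42 | 2.22 | -0.20 |
| 3 | 5.36 | 6.00 | +0.64 | 2.52 | 2.22 | -0.30 |
| 6 | 6.00 | 6.00 | 0.00 | 2.82 | 2.22 | -0.60 |
| 8 | 6.43 | 6.00 | -0.43 | 3.02 | 2.22 | -0.80 |

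Differences are test minus control, so a negative value favours the package. The all-children contrast favours it in every row. The case-only contrast takes either sign, or zero, although severity is unchanged throughout.

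**Break-even.** If prevented cases have r times the severity of the others, the two case-only means are equal when the package multiplies severity in the remaining cases by (0.37 + 0.10r) / 0.47. For r = 1/6, 1/3 and 1/2 this is 0.823, 0.858 and 0.894. The package must then cut severity by about 18%, 14% or 11% before the case-only comparison favours it at all.

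**Simulation** (510 per arm; counts in cases 1 + negative binomial with shape 1.5, assumed; 3,000 runs; no severity effect unless stated):

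- m = 2: the case-only contrast favours control in 97% of trials, significantly in 48%.
- m = 2 with a true 10% cut in severity: it favours control in 72%.
- m = 6: it favours control in 51%, significantly in 2.6%.
- m = 8: it favours control in 19%, and significantly favours the package in 14%.

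**The case against.** The strongest defence is that the caries-free children are not discarded. All of them enter the primary binary analysis, and any caries followed by surfaces given caries is the familiar two-part description of a count with many zeros. The all-children mean is the product of the parts: in the m = 2 row, 0.47 × 5.15 = 2.42 and 0.37 × 6.00 = 2.22. This stands as far as it goes. But the article never combines the parts into an overall contrast, and it tests the second part as an outcome in its own right, under an objective that attributes the result to the package.

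A second defence is that every surface mean above is assumed. That is correct. A reader might infer that the planned analysis will show harm, and the documents do not support that. Reversal needs prevented cases to be milder than the rest and too small a severity effect to offset it. With equal severity there is no bias in this illustration, and with more severe prevented cases the bias favours the package.

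Three other inferences also go too far:

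- **Intention to treat.** A reader might see a flat contradiction. The article does not define the term, and nothing moves a child out of the allocated arm. The restriction gives up the balance that the principle protects, which is a tension.
- **Economic analysis.** A reader might assume that cost per surface avoided uses the case-only count. The text does not say so, and a surface avoided can naturally include those of a child who stayed caries free. The passage is ambiguous.
- **Rank.** Outcome measures lists this outcome first among the secondaries, but the article sets no hierarchy.

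**Conclusion.** The point holds and should be fixed. The restriction is written into the objective and the outcome definition, so it is not a detail left to an analysis plan. That the comparison is not protected by randomisation follows from the article alone: all children start caries free, the subset is defined by the primary outcome, and the trial expects that outcome to differ by 10 percentage points. On its figures the comparison uses about 428 of 1,020 evaluable children. The 21% figure for control cases also needs the assumption that the package causes no caries.

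The size and direction of the bias rest on assumed severities. Over the range shown, the case-only difference goes from +1.06 to -0.43 surfaces when the package has no effect on severity. The primary outcome, its sample size and its logistic analysis are unaffected. With one secondary outcome concerned and a repair that needs no new data, this is a should-fix.

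**What to change.** 1. In the Abstract, Trial Objectives and Outcome measures, define the between-arm outcome as the number of carious surfaces in the primary dentition in all randomised children examined at 3 years, with 0 for those still caries free.
2. In Statistical analysis, name a negative binomial model for this count, or a two-part model whose parts are combined into an overall contrast of means, with the planned covariates. Report the ratio and the difference in means with 95% confidence intervals.
3. Keep the mean among caries-active children as a descriptive figure by arm, without a p-value or a causal claim.
4. In the economic paragraph, state that surfaces avoided are counted over all children.

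The cost is rewording in four places and one count model. The 3-year examination already planned for the primary outcome supplies the data, and the sample size does not change.
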